#### Baseline 2 evaluation and first treatment

Participants recommended for inclusion at case review return for the BL2 screening evaluation. This includes review of informed consent and completion of a self-report questionnaire. Headache diaries completed during the 4-week baseline period are collected, and eligibility is confirmed using checklists. Eligible patients are randomly assigned to one of 4 treatment groups by blinded study staff, receive their first of 18 treatments, and begin the second headache diary.

### Treatment allocation and concealment

An adaptive computer-generated rank-minimization scheme is used to allocate eligible participants to treatment [34]. The computer program balances 7 blocking variables separately for each of the 2 sites and is stratified by the presence of infrequent migraine headache: age, gender, CGH frequency and intensity, previous experience and confidence in SMT and professional massage therapy, and concomitant tension-type headache. Allocation concealment is protected by the use of balancing variables for rank minimization collected immediately prior to enrollment. Also, the number of participants previously randomized to each group is concealed from the study personnel involved in eligibility determination.

A computer generated random allocation sequence secured in sequentially numbered, opaque envelopes randomized within blocks is used to randomize the first several participants at each site to provide a “seed” group of participants for the dynamic allocation program. Envelopes are also used in the rare case of rank minimization program malfunction. Envelopes are created by the study statistician such that treatment allocation and block sizes are concealed from all study personnel.

### Interventions

Treatments are provided at university-affiliated clinics by licensed chiropractors with 6–35 years of clinical experience. At the Minnesota site, treatments are provided in a university research clinic. Treatments at the Oregon site are provided at one university clinic and 9 private chiropractic clinics. Participants commit to three, 10-min visits per week for 6 weeks (18 visits total), and the 10-min visits are standardized across sites. In the first 5 min, a moist hot pack is applied to relax neck and upper back musculature; cold packs are used for acute exacerbations. During this time, the chiropractor conducts a brief history, including subjective headache and/or neck complaints, patient progress, complications and medication changes. In the remaining 5 min, a standardized exam of the cervical and upper thoracic spine and musculature (occiput to 3^rd^ thoracic vertebra) is performed to identify sites of joint dysfunction to be treated. This includes manual palpation for segmental motion restriction, tenderness, and osseous asymmetry, as well as decreased global range of motion [35]. The study treatment is then delivered (Table 3). No other care is provided.

**Table 3 Tab3:** Treatment interventions

Intervention	Spinal manipulation therapy	Light massage therapy
Type	High Velocity, low amplitude Low Velocity, low amplitude (older patients or acute exacerbations only)	Gentle effleurage (gliding) Gentle petrissage (kneading)
Location	Cervical spine (Occiput -C7) Thoracic spine (T1-T3)	Cervical spine musculature (Occiput -C7) Thoracic spine musculature (T1-T3)
Design & delivery format	Individualized: spinal levels treated, technique position (e.g., seated, supine, prone)	Individualized: site of pain/dysfunction
		Prone position
Delivery method	One-on-one treatment visit	One-on-one treatment visit
Dose	10 min 3 visits per week for 6 weeks	10 min 3 visits per week for 6 weeks

To minimize intervention bias and confounding by contextual effects introduced by the provider during care, chiropractors are trained to interact with patients with equal enthusiasm for treatments across groups. Data regarding patients’ perceptions of their provider’s enthusiasm and confidence in the assigned study care are collected on questionnaires during and immediately following treatment (week 6) [26].

Standardized forms are used to document treatment procedures and side effects, and all forms are reviewed for protocol deviations and adverse events. Participants are asked to refrain from seeking care for their CGH and neck pain from other providers during the baseline and treatment periods; however, abortive analgesics are permitted as needed. Outside care is unrestricted following the treatment phase; data regarding non-study care is collected on self-report questionnaires.

Treatment providers are trained and certified to ensure standardization in intervention and documentation across study sites. Quality assurance includes meetings with providers to review treatment protocols and discuss uniform enthusiasm for both interventions. Meetings occur quarterly in Year 1 and biannually thereafter to ensure uniformity of care. Quality control measures are implemented to ensure compliance with the study protocol. Specifically, treatment forms are reviewed for completion after each visit, and all clinicians are observed at predetermined intervals throughout the active treatment phase. Following investigator, or designee observations, providers are recertified monthly in Year 1 and quarterly thereafter. Further, participants’ perception of their clinicians’ enthusiasm for care is used to give feedback to clinicians if imbalances across treatment groups are found.

#### Spinal manipulation

Spinal manipulation therapy (SMT) consists of the diversified thrust maneuver as described by Peterson and Bergmann [35]. The need for SMT is assessed at each visit via patient progress and a manual cervical palpation exam [35]. The clinician documents the sites of dysfunction and manipulates some or all dysfunctional regions based on the patient’s tolerance. SMT is not performed if there are no signs of joint dysfunction (i.e., palpable joint pain and/or restriction) or if a new contraindication exists. Modifications to high velocity, low amplitude manipulations are made for older participants and those with acute exacerbations (i.e., low-velocity, low-amplitude mobilization) [35]. Other chiropractic techniques are not permitted.

#### Light massage

Light massage consists of gentle effleurage and pétrissage applied to the neck and shoulder muscles [35, 36]. Clinicians use massage lotion, focus on the site of pain and dysfunction, and gently squeeze tender points to reinforce the sensation of therapy. Manual trigger point therapy is not permitted. Dose–response trials require a manual comparison group to control for attention and therapeutic touch, in this case visits without spinal manipulation therapy. In a trial comparing SMT and light massage, a minimal light massage was credible to participants [29].

#### Treatment dose

Participants are randomized to one of four doses (*n* = 64 per group): 0, 6, 12, or 18 SMT visits. All participants are assigned 18 total visits. When participants do not receive the index therapy (SMT), they receive the control therapy (light massage).

### Data collection

Patient self-reported outcomes are collected at baseline and 6, 12, 24, 39, and 52 weeks post randomization using headache diaries and questionnaires. Objective spinal biomechanical outcomes and pain pressure thresholds are collected at BL1 and at 6 weeks (end of treatment). Qualitative interviews are also conducted at the end of treatment. Study data is managed using Research Electronic Data Capture (REDCap) tools hosted at the University of Western States [37].

#### Headache diary

The International Headache Society (IHS) recommends using a daily headache diary to capture headache outcomes in efficacy trials [38]. An electronic diary, the preferred method, is sent to participants using a Short Message Service (SMS) or email response (SMS-Track ApS, Denmark https://www.sms-track.com/). Paper diaries are provided to participants without daily Internet or mobile phone access and are used as a back-up when the electronic platform is not available. Enrolled participants complete 6 headache diaries: one at baseline (to determine study eligibility), one during the treatment phase, and four during the follow-up phase. Diary questions are found in Table 4.

**Table 4 Tab4:** Diary questions

Diary questions	Response options
1. Did you take medication for a neck-related headache today?	1. Yes or No
2. Did you have a neck-related headache today?	2. Yes or No
3. If yes, rate your neck-related headache today?	3. 11-box numerical rating scale (0 = no pain, 10 = worst pain possible)
4. Did you have a headache not related to your neck?	4. Yes or No

Email or SMS options are available to participants depending on patient preferences. Automatic SMS messages (i.e., text-messages) or emails are sent to participants each night during the data collection period, and participants are given 24 h to respond. Participants who fail to respond during the designated time period cannot retroactively complete the diary. For those whose preference is email, 1 email is sent to the participant’s preferred address containing four questions (Table 4). Participants respond to the questions, submit their responses, and receive a thank you notification confirming successful delivery and data capture. Participants who chose the SMS option receive four individual SMS messages, one for each of the four questions. Paper diaries are mailed in advance.

### Outcomes

#### Primary aim: dose–response

##### CGH frequency

The primary outcome measure is self-reported CGH frequency, measured as the number of days with CGH in the 4 weeks prior to weeks 12 and 24 using a headache diary. The IHS guidelines for controlled trials recommend headache frequency as the most appropriate primary measure in efficacy trials [38]. Participants are also asked to recall the number of CGH days in the past 4 weeks on questionnaires, which are used as backup to the diaries. These time points were chosen to include short and long-term primary outcomes. CGH frequency measures at 6, 39, and 52 weeks are secondary outcomes (Table 5).

**Table 5 Tab5:** Data collection schedule

Outcomes	Variables	BL1	BL2	2W	6W	12W	24W	39W	52W
Background	Demographics; comorbidities	Q							
	Duration of episode; history of SMT and massage care		Q						
Primary Objective	Dose-Response								
Headache	CGH frequency in 4 weeks prior	Q	D, Q		D, Q	D, Q	D, Q	D, Q	D, Q
	CGH pain	Q	D, Q		D, Q	D, Q	D, Q	D, Q	D, Q
	CGH disability		Q		Q	Q	Q	Q	Q
	CGH improvement: pain, global perceived effect				Q	Q	Q	Q	Q
	Other headache days		D, Q		D, Q	D, Q	D, Q	D, Q	D, Q
Neck Pain	Frequency (days) of neck pain	Q	Q		Q	Q	Q	Q	Q
Quality of Life	EuroQol-5D		Q			Q	Q	Q	Q
Satisfaction	Likert Scale, success of care				Q	Q	Q	Q	Q
Medication	Frequency of prescription and non-prescription medication (days)		D, Q		D, Q	D, Q	D, Q	D, Q	D, Q
Outside Care	CGH care from external providers		Q	Q	Q	Q	Q	Q	Q
Objective Measures	Kinematics and cervical segmental joint function	X			X				
Secondary Objective	Cost Effectiveness								
Healthcare Utilization and lost productivity			Q		Q	Q	Q	Q	Q
Utilities	Quality-adjusted life years EuroQol-5D		Q			Q	Q	Q	Q
Outcomes	CGH frequency (days) and intensity (in last 4 wks)	Q	D, Q		D	D	D	D	D
Tertiary Objective	Effects of Expectations								
Quantitative	Confidence in treatment success		Q	Q	Q	Q	Q	Q	Q
	Perceptions of the Patient-provider encounter			Q	Q				
Qualitative	Meaning, constructs of expectations				I				

Key: *BL* baseline, *SMT* spinal manipulation therapy, *W* weeks, *CGH* cervicogenic headache, *Q* questionnaire, *D* diary, *I* interview, *X* indicates occurrence

##### CGH pain

Patient-rated headache intensity is the principal secondary outcome and is measured using the valid and reliable 11-point numerical rating scale [39]. Intensity is the average of daily pain rated over four weeks on the headache diary. Diaries are backed-up by participants recall of their average pain over the last 4 weeks collected on the questionnaires using the same scale. Evaluation of headache pain is recommended by the IHS [38].

##### Disability

Patients rate their headache-related disability using the valid and reliable Headache Impact Test (HIT-6) [40]. This 6-item survey is administered at BL2 and following the intervention phase.

##### Quality of life

This is collected using the EuroQol-5D, a multi-attribute utility scale. The 5 dimensions (mobility, self-care, usual activities, pain/discomfort, and anxiety/depression) are evaluated with three levels (no, moderate or severe problem). This will be used to compute quality-adjusted life years for the cost-utility analysis. This is a commonly employed instrument with sound psychometric properties [41, 42].

##### Improvement

Patient-rated global improvement is determined by asking participants to compare their headache condition to what it was before study treatment on a 9-point ordinal scale ranging from no symptoms (100% improvement) to as bad as it could be (100% worse). Improvement has been shown to be reliable and responsive [43]. Improvement in CGH pain is also evaluated on a −10 to +10 numerical rating scale.

##### Other headache days

Participants indicate whether they have headaches other than cervicogenic on the headache diary. The sum of headache days in the last 4 weeks is used.

##### Neck pain frequency

Self-reported neck pain frequency, measured in days, is collected on the mailed questionnaires. Participants are asked if they had neck pain over the last four weeks (yes or no), and if so, how many days they had neck pain (1–28 days).

##### Neck pain

Participants are asked to rate their average neck pain over the past 4 weeks using the valid and reliable 11-box numerical rating scale (0 = no pain, 10 worse pain possible) [39]. Participants with spinal problems consider pain to be an important outcome measure [44].

##### Satisfaction

Participants overall satisfaction with treatment is measured using a 6-point Likert scale ranging from extremely dissatisfied to extremely satisfied. This scale is adapted from the Interstudy’s Low Back Pain TyPE Spec [45].

##### Medication use

Participants report frequency of over-the-counter and prescription medication use on diaries and questionnaires. The daily diary asks: “Did you take any medication for a neck-related headache today?” (yes or no).

##### Outside care

Discretionary professional care outside the study, including emergency care and hospitalizations rendered for CGH, is captured on questionnaires. Participants are asked, “In the past four weeks, have you seen any healthcare provider for your neck related headaches?” (yes or no). If yes, participants indicate which type of provider they visited and the frequency of visits.

##### Cervical kinematics

These are evaluated using the Zebris CMS-HS Spine Motion Analyzer (Zebris Inc., Isny im Allgau, Germany) and a modified protocol described by Wang [46]. This reliable and accurate tool has been used in other RCTs [46–49]. Flexion, extension, lateral flexion and rotation, coupled out of plane motion, and maximum accelerations and velocities in these planes are recorded.

##### Pressure pain threshold

These are evaluated using a hand-held algometer (Wagner Instruments. Force One™ Digital Force Gage. FDIX. Greenwich, CT, USA) applied to standardized locations along the cervical and upper thoracic spine. In addition, pain pressure thresholds are assessed at areas identified as clinically important by the examiner using manual palpation techniques [35]. Examiners are trained across sites to apply pressure at a rate of approximately 1kg/s until pain is elicited. This is a reliable method for ascertaining pain pressure thresholds [50] and is shown to be associated with outcomes [30].

#### Secondary aim: cost-effectiveness

Direct and indirect healthcare costs are included. Direct costs are determined from health services utilized and indirect costs from lost productivity [51].

##### Healthcare utilization

The utilization of health services for headache not provided in the study are captured on questionnaires at all-time points. Health services include physician and other provider visits, hospital services, prescription and non-prescription medication, advanced imaging, and classes/programs attended. Questions from the Community Tracking Study Household Survey [52] are used to capture provider and hospital services. Information for other service is ascertained using an instrument developed for a low back pain study [53]; this was also used in a CGH pilot study [29].

##### Lost productivity

Indirect costs, which include lost workdays and productivity, are assessed using three questions from the National Health Interview Survey [54]. Lost productivity data is captured on questionnaires.

#### Tertiary AIM: effects of expectations

##### Qualitative interviews

One-on-one (face to face), semi-structured qualitative interviews are conducted by trained research staff at week 6. An interview schedule is used to direct the interviews and keep interviewers on track with the study’s objective. Participants are asked about their treatment views, expectations and lived experience with headaches. Questions start broadly and are followed-up with probing questions to elicit additional information.

##### Confidence in treatment success

This is measured using a 7-point Likert scale adapted from the Interstudy’s Low Back Pain TyPE Spec [45]. Potential success is assessed at baseline and week 2. Confidence that assigned treatment is working is measured at all follow-up time points.

##### Perceptions of the patient-provider encounter

Perceptions are evaluated at weeks 2 and 6 and are used to determine the effect of the patient-provider experience on expectations and outcomes [26, 29]. The instrument used is based on the satisfaction questionnaire by Cherkin et al. [55, 56]. Specifically, participants are asked about their level of agreement with statements about their perception of the treating chiropractors’ adequate time spent listening, comfort with dealing with CGH, enthusiasm about the treatment program, and confidence that treatment will work.

### Blinding

Research staff who perform clinical and objective examinations and data entry are blinded to treatment assignment. Providers and participants are initially blinded to dose and the treatment hypotheses; however, treatment dose becomes apparent over time. Due to the nature of the SMT and light massage treatments, providers and patients are not blinded to treatments at each visit. Qualitative interviewers and project managers at both sites are not blinded.

### Adverse events

Incomplete reporting of adverse events remains a problem in clinical trials investigating therapies for CGH [57]. To address this, we use standardized and systematic recording and reporting of unanticipated and anticipated events. Enrolled participants are queried at each treatment visit and following the treatment phase (week 6) about problems, complications to care, or adverse events since their last appointment. During the follow-up data collection phase, participants are asked whether they spent >24 h in bed and/or if they were hospitalized for any reason on questionnaires; research staff contact participants by phone if an event occurred. Documentation of such events occurs on a standardized case report form which includes a severity rating, relatedness of the event to study participation, and whether the event was anticipated. Further, participants are asked to report serious adverse events to the study investigators or research staff. Oversight authorities (i.e., IRBs, funding agency) are informed about serious, reportable adverse events within three business days of the event first being identified. Non-reportable events are summarized for the data safety and monitoring board annually.

### Analysis plan

#### Primary aim: dose–response

##### Primary analysis

Both primary and secondary variables will be regressed on dose, baseline value of the outcome, site indicator (Portland or Minneapolis), and 6 baseline balancing variables used for randomization in the rank-order minimization computer program (CGH days, CGH pain, gender, age, tension-type headache indicator, and differential confidence in success of SMT and LM) [58]. The analysis will be stratified by migraine headache. Dose will be included in two separate ways: as a linear/nonlinear function and as a set of indicator variables to make comparisons between the SMT groups and the control group. Seemingly unrelated (simultaneous) regression by Zellner [59] will be used in the analysis for the individual time points [60]. For the primary outcomes only, longitudinal effects across all follow-ups will be modeled with generalized estimating equations to account for within-person correlation between time points [60]. An intention-to-treat analysis will be conducted with participants included in the original allocation group. Missing data will be imputed by interpolating between adjacent times, or by carrying forward when there is no subsequent data. An intention-to-treat analysis will be conducted with participants included in the original allocation group. Missing data will be imputed by interpolating between adjacent times, or by carrying forward when there is no subsequent data. This method was used in our pilot study [28] and full-scale, dose–response randomized trial on manipulation for low back pain [61] where the quantity of missing data was reasonably small. Sensitivity analyses 1) using multiple imputation and 2) excluding imputed data will be performed to assess the impact of missing data [62, 63].

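### The primary analysis fills missing headache days by interpolation or carry-forward, which can bias the week-12 and week-24 dose effects; multiple imputation, planned only as a sensitivity analysis, should be primary

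*Protocol article*

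**What the plan says.** The primary outcome is cervicogenic headache (CGH) frequency, "measured as the number of days with CGH in the 4 weeks prior to weeks 12 and 24 using a headache diary" (protocol article, CGH frequency). Patient-reported outcomes are "collected at baseline and 6, 12, 24, 39, and 52 weeks post randomization using headache diaries and questionnaires" (Data collection). Questionnaire recall of headache days over the same four weeks is also collected, and these answers are items "which are used as backup to the diaries" (CGH frequency).

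The section Primary analysis fixes how gaps are handled: "Missing data will be imputed by interpolating between adjacent times, or by carrying forward when there is no subsequent data". The reason given is that the same method served in a pilot study and in a low back pain dose-response trial, "where the quantity of missing data was reasonably small". No expected rate is given for this trial. The section then adds: "Sensitivity analyses 1) using multiple imputation and 2) excluding imputed data will be performed to assess the impact of missing data". Individual time points are analysed by "Seemingly unrelated (simultaneous) regression by Zellner". For the primary outcomes, "longitudinal effects across all follow-ups will be modeled with generalized estimating equations to account for within-person correlation between time points".

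The section Interventions sets a six-week treatment course. It asks participants to avoid other care during the baseline and treatment periods and lifts that restriction afterwards.

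**The concern.** The headline result rests on one deterministic value per gap. Both rules carry a strong assumption. Carry-forward assumes no change after the last observed visit, and interpolation assumes a straight line between the neighbouring visits.

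The carry-forward assumption fits this trial badly. A participant lost after week 6 contributes the end-of-treatment value at both week 12 and week 24. Those time points were chosen to show short-term and long-term effect once treatment has stopped. The imputed value presupposes that the week-6 effect lasted, and it comes from a phase with different rules on outside care. If the effect fades, a dose effect from week 6 is moved into week 24. If the effect grows, or if baseline values are carried forward, the dose effect is diluted. If dropout differs by dose, a slope can appear where there is none.

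The justification rests on how much data went missing in other studies, one of them in another condition. The choice therefore matters most in the situation the article does not address, which is more missing data than hoped for.

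**Working it through.** **Inputs from the article.** 64 per group and 256 in total, residual SD 7, two-sided 0.05, 80% power, detectable slope 1.1 days per dose step, detectable two-group difference 3.5 days (Power analysis and sample size). Visits at weeks 6, 12, 24, 39 and 52.

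**Assumptions, not in the article.** Dropout of 5%, 10% or 20%; between-visit correlation 0.6; the time courses named below. A negative slope means fewer headache days per dose step.

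**The plan's own figures.** With doses coded 0 to 3, Sxx = 64 × 5 = 320 and SE(slope) = 7/√320 = 0.391.
- Detectable slope = (1.960 + 0.842) × 0.391 = 1.096, and power at 1.1 is 0.803.
- For two groups, SE = 7 × √(2/64) = 1.237 and power at 3.5 is 0.807.

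Both stated figures reproduce, with all 256 participants counted as observed.

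**Carry-forward bias with a fading effect.** Let a proportion d drop out independently of outcome and dose, half after week 6 and half after week 12. Let the true slopes be s6, s12 and s24. The expected carry-forward slope at week 24 is (1 − d)·s24 + (d/2)·s6 + (d/2)·s12. With slopes -2, -1 and 0 this is −1.5d.

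| Dropout | −1.5d | Simulated week-24 slope (truth 0) | Simulated rejection at nominal 5% |
|---|---|---|---|
| 5% | -0.075 | -0.07 | about 5% |
| 10% | -0.15 | -0.14 to -0.16 | 6.5 to 6.9% |
| 20% | -0.30 | -0.30 to -0.32 | about 12% |

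The rejection rates follow from the shift. At 20%, 0.30/0.396 = 0.76 standard errors, which gives about 12%.

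Multiple imputation in the same setting gave slopes of 0.01, -0.01 and -0.02, with rejection of 5.1%, 5.8% and 5.5%. When dropout also depended on the week-6 value, coverage at 20% dropout was 87% with carry-forward and 95% with multiple imputation.

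**The same formula with a smaller early effect.** Slopes of -1.1, -0.55 and 0 give −0.825d, which is -0.04, -0.08 and -0.17. Simulated values were -0.03, -0.09 and -0.17, with rejection of 4.5%, 5.0% and 7.2%.

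**Other time courses (simulated).**
- Sustained slope of -1.1, dropout only after week 6: -1.10 at 10% and -1.09 at 20%, so essentially no bias.
- Sustained slope of -1.1, dropout that can also begin before week 6 (baseline carried forward): about -1.05 at 10% and -1.03 at 20%, a dilution.
- Growing effect, 20% dropout: week-24 slope -0.95 against a true -1.10.
- Effect waning from -1.8 to -1.1 by week 24, 20% dropout including before week 6: -1.10 against -1.10, because two errors cancel.
- No effect, equal dropout: no bias.
- No effect, dropout three times higher in the 0-visit group than in the 18-visit group (20% on average), assumed mean fall of 4 days in controls: a false slope of about -0.10.

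**Interpolation.** A missing week 12 between weeks 6 and 24 becomes (12/18) × week 6 + (6/18) × week 24. Under slopes -2, -1 and 0 its expected slope is 0.667 × (-2) + 0.333 × 0 = -1.33 against a true -1. Interpolation is therefore unbiased for the slope only where the change in effect is linear over the gap.

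**Standard errors.** Across scenarios the model SE divided by the empirical SD of the imputed-data slope was 0.97 to 1.02. At 20% dropout in the fading scenario it was 0.396 against 0.392. For comparison, the SE was 0.433 with multiple imputation and 0.437 with complete cases (0.391/√0.8 = 0.437). With no effect at any visit and equal dropout, rejection was 4.9 to 5.3%.

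**Limits.** The simulations used ordinary regression. They did not cover the seemingly unrelated regression, the estimating equations or the 0-to-28-day bound.

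**The case against.** The strongest case against the point is that the plan already contains its remedy. Multiple imputation and exclusion of imputed data are both prespecified, so a reader would see any discrepancy. Questionnaire recall replaces missing diaries at each follow-up, which reduces how often imputation is needed, and carry-forward applies only where no later data exist. At 5 to 10% dropout the bias is small beside the design slope of 1.1 days. The -2/-1/0 course is also a harsh one, since its week-6 slope is nearly twice the design slope and it fades completely.

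All of that stands, and it lowers the severity. It does not settle the matter. Recall cannot help for a participant who returns neither diary nor questionnaire, and if the analyses disagree the plan makes the less defensible one the headline.

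A reader might also infer stronger claims that the documents do not support:
- *That the dose effects are certainly biased.* The article gives no dropout rate, pattern by dose or time course. Some plausible combinations produce no bias, and others dilute the effect.
- *That standard errors are too small, so intervals are too narrow for that reason alone.* Each imputed value uses only that participant's own visits, so records stay independent and the regression SE is about right for this estimator. The ratio 1/√(1 − m) − 1, with m the proportion missing, is about 5% at 10% missing and 12% at 20%. It compares the imputed-data SE with the complete-case SE and does not measure an error in the former. Undercoverage comes through bias.
- *That excluding imputed data must drop everyone with any missing visit.* The article does not specify the implementation. Each time point can be fitted on its own observed rows, and estimating equations can use incomplete participants.

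**Conclusion.** The point holds in a conditional form and should be fixed, though it is not a fatal flaw. The plan makes deterministic single imputation primary in a trial whose primary time points fall after treatment ends, so the imputation rule assumes part of the answer.

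Under the assumed complete fade from a week-6 slope of -2, the false week-24 slope is about -0.07, -0.14 and -0.3 day per dose step at 5%, 10% and 20% dropout. At 20% the false-positive rate is about 12%. With a week-6 slope of -1.1 the bias is roughly half as large. It is near zero when the effect is sustained after week 6, or absent with equal dropout. These sizes rest on assumed dropout rates, assumed time courses and a correlation of 0.6. The type I error is not inflated by the standard error itself.

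**What to change.** Reverse the order of the analyses. Make multiple imputation primary, imputing from dose group, baseline covariates and all observed follow-ups and combining with Rubin's rules. A likelihood-based repeated-measures model on all observed visits, with dose-by-visit terms and an unstructured covariance, would serve equally well. Keep interpolation and carry-forward as a sensitivity analysis alongside the exclusion of imputed data.

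The cost is a change of wording, a little more analysis work and slightly wider intervals (at 20% dropout in the fading scenario, SE 0.433 against 0.396). No new data are needed. The article reports follow-up as ongoing and plans no interim analyses, so on its own account the change could be prespecified before results are known.
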